#### **10.4 Subgroup Analysis**

The immunogenicity analysis will be conducted in each sequential vaccination cohort (1-3 months, 4-6 months and  $\geq$ 6 months after two doses).

#### **10.5 Interim Analysis**

No interim analysis will be planned in this study.

#### **10.6 Multiplicity**

Only when both non-inferiority conclusion in 4-fold rise and GMT after vaccination between treatment and control groups are achieved, the non-inferiority between the two groups will be concluded finally. Therefore, no multiplicity adjustment is required here.

#### **10.7 Handling of Missing Data**

In FAS immunogenicity analysis, LOCF (Last Observation Carried Forward) method will be used to impute the missing values in antibody data after vaccination. And other

immunogenicity endpoints will be derived from the imputed data. The missing data in safety and immunogenicity persistence evaluation will be not imputed.

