| 
Note:
 
1) Blood collection window at 14 days, 28 days is +10 days, blood collection window at 3M, 6M, 9M, 12M is +30 days.
 
2) If the blood sample test results show that the antibody level is too low after the full immunization, blood collection at subsequent time points will not be carried out.
 |                                                                                                                                                                                                                                                                                                                                                                                                                                                                                                                                                                                                                                                                                                                                                                                                                                                                                                                                                                                                                                                                                                                                                                                                                                                                                                                                                                                                                  |  |      |  |                          |

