#### **3.2. Secondary Objectives**

To evaluate the safety of recombinant COVID-19 vaccine (CHO cells) and inactivated COVID-19 vaccine (Vero cells) 28 days after sequential vaccination of one dose in population  $\geq 18$  years of age.

To evaluate the optimal immunization schedule of sequential vaccination of recombinant COVID-19 vaccine (CHO cells) in population  $\geq 18$  years of age.

To evaluate the immune persistence of sequential vaccination of recombinant COVID-19 vaccine (CHO cells) and inactivated COVID-19 vaccine (Vero cells) in population  $\geq 18$  years of

age.

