1) Blood collection window at 14 days, 28 days is +10 days, blood collection window at 3M, 6M, 9M, 12M is +30 days.

2) If the blood sample test results show that the antibody level is too low after the full immunization, blood collections at subsequent time points will not be carried out.

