#### **4.3.3 Immune Persistence Endpoints:**

GMT of anti-SARS-CoV-2 neutralizing antibody and IgG antibody, the proportions of neutralizing antibody titered  $\geq 1:16$ ,  $\geq 1:32$  and  $\geq 1:64$  at 3 months, 6 months, 9 months and 12 months after full course of immunization,

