### **10. STATISTICAL CONSIDERATIONS**

#### **10.1 Sample Size Considerations**

Assume 4-fold rise rate after sequential vaccination achieve 85%, 208 subjects in each arm will be required to have 80% power to conclude non-inferiority with margin of -10% and one-sided significance level of 2.5% using Miettinen & Nurminen method.

Equal GMT after sequential immunization is assumed, and standard deviation of GMT after log10 transformation is considered to be 0.7. 250 subjects in each arm will be required to have 80% power to conclude non-inferiority with margin of 2/3 and one-sided significance level of 2.5%.

Considering about 15%~20% drop-out rate, 600 subjects in three sequential cohorts (1-3 months, 4-6 months and ≥6 months after 2 doses), and 1800 subjects (900 subjects in test and control groups respectively) in total are planned to enroll.

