#### **10.2 Analysis Set**

Full Analysis Set (FAS): It includes all randomized participants who follow ITT principle, receive 1 dose of vaccine, and have valid immunogenicity data before the first dose.

Per-Protocol Set (PPS): It includes all participants who do not violate the inclusion criteria/exclusion criteria, receive 1 dose of vaccine, and have both valid pre- and post-vaccination immunogenicity data. PPS will be defined for immunogenicity evaluations 14 and 28 days after sequential vaccination, respectively.

Immunogenicity Persistence Set (IPS): It include the participants who are collected

with blood samples at each time point for immunogenicity persistence evaluation and with valid antibody data. Define the IPS for immunogenicity for 3, 6, 9, 12, 18 and 24 months after sequential immunization respectively.

Safety Set (SS): It includes all participants who receive one dose of vaccination.

In immunogenicity analysis, the participant who takes the vaccine erroneously will be included as randomized, and the safety data will be analyzed as treated.

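### Persistence GMTs are visit-by-visit available-case means, unbiased only if missing samples are unrelated to titre, and the protocol's own low-antibody stopping note puts that in doubt

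*Protocol*

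**What the plan says.** Section 3.2 makes immune persistence of both vaccines a secondary objective. Section 4.3.3 gives the endpoints: neutralizing and IgG GMTs, and the proportions at or above 1:16, 1:32 and 1:64, at "3 months, 6 months, 9 months and 12 months after full course of immunization".

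Section 10.2 limits the persistence set (IPS) to participants "with blood samples at each time point for immunogenicity persistence evaluation and with valid antibody data". The next sentence makes it visit-specific: "Define the IPS for immunogenicity for 3, 6, 9, 12, 18 and 24 months after sequential immunization respectively". (Months 18 and 24 are not in the blood schedule of Table 1.) Section 10.7 adds: "The missing data in safety and immunogenicity persistence evaluation will be not imputed". The LOCF rule in the same section covers the FAS immunogenicity analysis, not persistence.

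Section 10.3.3 describes an ANCOVA, descriptive GMTs and t-tests on log titres. It names no longitudinal model.

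Note 2 to Table 1 in section 4.2 provides that if test results show the "antibody level is too low after the full immunization, blood collections at subsequent time points will not be carried out". The synopsis carries the same note. Neither place gives a threshold or says whose antibody level counts, the subject's or the group's.

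**The concern.** Each visit's GMT is a mean over whoever has a valid titre at that visit. A fall, or a lack of fall, from month 3 to month 12 then mixes waning with a change in who is measured. The day-14 and day-28 titres, which are informative about later ones, play no part for subjects who drop out of the later sets.

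This would matter little if samples were missing at random with respect to titre. But the stopping note ties later sampling to an earlier antibody result. If it is applied to individuals, low titres leave the later visits by design and durability looks better than it is. If the weaker arm loses more low titres, the arm comparison is distorted as well.

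**Working it through.** **The SD.** Section 10.1 states that the standard deviation after log10 "transformation is considered to be 0.7. 250 subjects in each arm will be required to have 80% power". Check: n = 2 × 0.7² × (1.960 + 0.842)² / 0.1761² = 248.1, so 249 per arm; the noncentral t version gives 250. The protocol's figure reproduces, and 0.7 is used below as the SD of a log10 titre. The protocol gives no figure for persistence. Its 15 to 20% drop-out allowance is not tied to a visit.

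**Titre-related loss in general.** Inputs other than the SD are assumptions:
- ρ, the correlation of day-28 and month-12 log titre: 0.3 to 0.8;
- loss by month 12: 10 to 30%;
- OR, the odds of loss per SD lower day-28 titre: 1.0 to 2.0.

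Let x be the standardised day-28 log titre and P(loss) = 1/(1 + exp(−a + x·ln OR)), with a chosen to give the stated overall loss. Let s be the mean of x among those retained. The available-case month-12 GMT is then too high by the factor 10^(ρ × 0.7 × s).

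- ρ 0.7, OR 1.65, loss 20%: s = 0.0963; shift 0.7 × 0.7 × 0.0963 = 0.0472; factor 10^0.0472 = 1.115.
- ρ 0.8, OR 2.0, loss 30%: s = 0.190; shift 0.8 × 0.7 × 0.190 = 0.1064; factor 10^0.1064 = 1.28.

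| ρ, OR | 10% loss | 20% loss | 30% loss |
|---|---|---|---|
| any, 1.0 | 1.00 | 1.00 | 1.00 |
| 0.3, 1.3 | 1.01 | 1.03 | 1.04 |
| 0.5, 1.65 | 1.04 | 1.08 | 1.12 |
| 0.7, 1.65 | 1.06 | 1.11 | 1.17 |
| 0.8, 2.0 | 1.09 | 1.18 | 1.28 |

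**Arm ratio.** The bias is the quotient of the two arms' factors. With the same ρ, OR, loss and SD in both arms it is 1. With the middle scenario in one arm and no dependence in the other, a true ratio of 1.00 becomes 1/1.115 = 0.90 (or its inverse, depending on the arm).

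**The stopping note, if applied per subject.** This is an illustration only. Assumed: day-28 GMT 60 or 120, a fall of 0.9 log10 by month 12, within-subject correlation 0.5 or 0.8, and no further samples after a titre below 1:4 or 1:16. Each scenario is 300 simulated data sets of 300 subjects. The last column is a maximum-likelihood estimate from all observed titres from day 28 on.

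| Day-28 GMT | Stop below | Still sampled at month 12 | True month-12 GMT | Available-case | Likelihood |
|---|---|---|---|---|---|
| 60 | 1:4 | 60–67% | 7.6 | 13.7–15.6 | 7.6–7.7 |
| 60 | 1:16 | 24–32% | 7.6 | 25.4–33.2 | 7.4–7.6 |
| 120 | 1:4 | 77–82% | 15.1 | 21.7–23.4 | 15.1–15.2 |
| 120 | 1:16 | 41–50% | 15.1 | 35.9–44.0 | 15.1–15.2 |

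The overstatement runs from 21.7/15.1 = 1.4 to 33.2/7.6 = 4.4. Treating 120 and 60 as two arms, a true ratio of 2.0 is seen as between 44.0/33.2 = 1.3 and 21.7/13.7 = 1.6.

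**The case against.** Ruling out imputation is not an error; a likelihood model imputes nothing, and its choice may sit in a statistical analysis plan that is not shown. That stands, and a reader who infers that nothing is done for missing titres goes beyond the text. What remains is that the protocol itself fixes visit-specific sets, which leave out subjects who have day-14 or day-28 titres but no later sample. A longitudinal model needs exactly those subjects.

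A reader might also infer that low responders will stop attending. No section says so: subjects are enrolled as healthy, the trial is blinded, and nothing says that individual titres are reported to them. The only titre-related cause of missing samples in the text is the stopping note, and it may be meant for a whole group. The 1.4- to 4.4-fold figures therefore illustrate one reading and are not an estimate for this trial.

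The near-perfect recovery by the likelihood estimate is partly built in, because stopping was simulated to depend only on observed titres. The model replaces one untestable assumption with a weaker one, and it does not yield the threshold proportions. Finally, the protocol states no hypothesis or margin for persistence. All of this stands and limits the weight of the point.

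**Conclusion.** The point holds in limited form. As written, persistence is an available-case analysis at each visit, valid only if missingness is unrelated to titre, and the stopping note gives a documented reason to doubt that. With SD 0.7 and the assumed ranges above, the month-12 GMT is overstated by a factor of 1.00 to about 1.28; no single value in that range can be singled out from the documents. If the stopping note were applied to individuals the inflation could be larger, by an amount that depends on a threshold the protocol does not give. The arm ratio is affected only if loss or its dependence on titre differs by arm. The consequence is confined to a secondary objective: the day-14 and day-28 non-inferiority conclusions are not affected.

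**What to change.** 1. Estimate persistence GMTs and GMT ratios from one likelihood-based repeated-measures model on all observed log titres from day 14 to month 12, with arm, visit, arm-by-visit, cohort and log pre-booster titre. Include subjects with day-14 or day-28 titres but no later sample. Keep the per-visit IPS summary as a descriptive table. The no-imputation rule in section 10.7 can stay.
2. For the proportions at or above 1:16, 1:32 and 1:64, add a sensitivity analysis in which subjects whose sampling was stopped for low antibody count as below threshold.
3. Reconcile the stopping note in the synopsis and section 4.2 with the persistence analysis, and state whether it applies per subject or per group and what antibody level triggers it.

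Cost: wording and standard SAS code, with no new samples or visits. The model relies on missing-at-random and approximate log-normality, and needs slightly more analysis work.

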## **11. ETHICAL AND REGULATORY MATTERS**

This clinical trial will be conducted by the Sponsor, the Investigator, and delegated Investigator staff and Sub-investigator, in accordance with consensus ethics principles derived from international ethics guidelines, including the Declaration of Helsinki, and the ICH guidelines for good clinical practice (GCP), all applicable laws, rules and regulations.

### **11.1. Ethics Committees and Regulatory Authorities**

The ICH-GCP (E6 (R2)) guidelines require that approval must be obtained from an Independent Ethics Committee (IEC) prior to participation of human subjects in research studies. Prior to the study onset, the protocol, informed consent, advertisements to be used for subject recruitment, and any other written information regarding this study to be provided to the subject or the subject's legal guardian must be approved by the IEC. Documentation of the relevant national IEC approval and of the IEC compliance with ICH Guideline E6 will be maintained by the site and will be available for review by the Sponsor or its designee or by the authorized members of regulatory agencies.

The respective Ethics Committees approvals should be signed by the IEC Chairman or designee and must identify the IEC name and address, the clinical protocol by title and/or protocol number and the date approval and/or favorable opinion was granted. Also, a list of the EC members who attended the meeting when the Protocol/ Protocol amendment was discussed, including names and qualifications, needs to be provided by the EC to the investigator or the sponsor/ his representative.

If any alterations, other than changes of administrative nature only, are made to the study protocol, a formal protocol amendment will be issued and submitted to relevant IEC for approval. The amendment will not be implemented until IEC approval, except in cases where immediate implementation is necessary to eliminate or prevent imminent hazard to the subjects.

In the same way, approval from regulatory authorities (RA) should be granted before beginning the study. The investigator or the sponsor representative must provide to the regulatory authorities the name and address of the EC along with a statement from the EC that it is organized according to GCP and the applicable laws and regulations. Amendments will be submitted to RA too for approval.

## **11.2. Responsibilities of the Sponsor**

The Sponsor of this clinical trial is responsible to regulatory authorities for taking all reasonable steps to ensure the proper conduct of the clinical trial as regards ethics, clinical trial protocol compliance, and integrity and validity of the data recorded on the e-CRFs. Thus, the main duty of the monitoring team is to help the Investigator and the Sponsor maintain a high level of ethical, scientific, technical and regulatory quality in all aspects of the clinical trial.

At regular intervals during the clinical trial, the site will be contacted, through monitoring visits, letters or telephone calls, by a representative of the monitoring team to review study progress, Investigator and subject compliance with clinical trial protocol requirements and any emergent problems. These monitoring visits will include but not be limited to review of the following aspects: subject informed consent, subject recruitment and follow-up, SAE documentation and reporting, AE documentation, IP allocation, subject compliance with the instructions, IP accountability, concomitant therapy use, and quality of data.

## **11.3. Responsibilities of the Investigator**

The Investigator is responsible for ensuring that the clinical study is performed in accordance with the protocol, the ethical principles that have their origin in the Declaration of Helsinki (version as of October 2013) as well as with the ICH Note for Guidance on Good Clinical Practice (ICH, Topic E6, R2, 2016), relevant site SOPs and applicable regulatory requirements. These documents state that the informed consent of subjects is an essential precondition for participation in the clinical study.

The Investigator is required to ensure compliance with all procedures required by the clinical trial protocol and with all study procedures provided by the Sponsor (including security rules). The Investigator agrees to provide reliable data and all information requested by the clinical trial protocol (with the help of the e-CRF, Discrepancy Resolution Form [DRF] or other appropriate instrument) in an accurate and legible manner according to the instructions provided and to ensure direct access to source documents by Sponsor representatives.

If any circuit includes transfer of data particular attention should be paid to the confidentiality of the subject's data to be transferred.

The Investigator may appoint such other individuals as he/she may deem appropriate as Sub-investigators to assist in the conduct of the clinical trial in accordance with the clinical trial protocol. All Sub-investigators shall be appointed and listed in a timely manner. The Sub-investigators will be supervised by and work under the responsibility of the Investigator. The Investigator will provide them with a copy of the clinical trial protocol and all necessary information.

In 1998, the US Food and Drug Administration (FDA) introduced a regulation (21 CFR, Part 54) entitled “Financial Disclosure by Clinical Investigators.” For studies conducted in any country that could result in a product submission to the FDA for marketing approval and which contribute significantly to the demonstration of efficacy and safety of the drug (named “covered studies” by the FDA), the Investigator and all sub-Investigators are obliged to disclose their financial interest which they or their spouses and dependent children may have in the Sponsor. This information is required during the study and until 12 months after its completion.

#### **11.4. Subject Information and Consent**

A prerequisite for a subject participating in the study is his/her or their legal representative or parent's/guardian's written informed consent. Adequate information must therefore be given to the subject by the Investigator/ designated personnel before informed consent is obtained. One or more Informed Consent Forms in the local language and prepared in accordance with the Note for Guidance on Good Clinical Practice (ICH, Topic E6 (R2)) will be provided by the Sponsor for the purpose of obtaining informed consent. In addition to this written information, the Investigator or his designate will inform the subject verbally. In doing so, the wording used will be chosen so that the information can be fully and readily understood by laypersons. The Informed Consent Form will be revised whenever important new information becomes available that may be relevant to the consent of subjects.

The subject must be informed that his/her personal trial-related data will be used by CNBG and his subsidiaries (sponsor) in accordance with the local data protection law. The level of disclosure must also be explained to the subject.

The subject must be informed that his/ her medical records may be examined by authorized monitors or Clinical Quality Assurance auditors appointed by CNBG and his subsidiaries (sponsor), by appropriate IRB / IEC members, and by inspectors from

---

regulatory authorities.

The Informed Consent Form must also be signed and personally dated by the subject and legal representative or parents/guardian and by the Investigator/person designated by the Investigator to conduct the informed consent discussion. Provision of consent will be confirmed in the eCRF by the Investigator. The signed and dated declaration of informed consent will remain at the Investigator's site and must be safely archived by the Investigator so that the forms can be retrieved at any time for monitoring, auditing and inspection purposes. A copy of the signed and dated information and consent should be provided to the subject prior to participation.

### **11.5. Compensation to Subjects**

Appropriate insurance coverage is provided by China National Biotech Group (CNBG) in line with legal requirements and GCP guidance. Details can be asked at the investigator's site (certificates and conditions in the Investigator Site File).

Insurance coverage will be provided by a local insurance provider.

### **11.6. Subject Confidentiality**

The investigator(s) will respect and protect the confidentiality of the subject in all possible ways. Subject identification, other than subject number, initials and date of birth, will not appear in any Case Report Form (eCRF) pages or other documents given to the Sponsor. Only the investigator and the persons authorized to verify the quality and integrity of the study will have access to subject records where the subject can be identified.

Ensure that the personal secrets of the subjects will not be disclosed under the conditions of testing, biological sample collection, reporting and publication, etc. Only the subject code, blood sample number, blood collection time and test index are recorded in the blood sample. It is strictly limited to the core testing personnel to obtain electronic or written copies.

### **11.7. Amendment to Subject Related Information**

Should a Protocol amendment become necessary, the subject information and consent form may need to be revised to reflect the changes to the Protocol. It is the responsibility of the investigator to ensure that an amended consent form is reviewed and has received approval/ favorable opinion from the IRB / IEC and CA and/or the regulatory authority has provided approval / has been notified (depending on local laws and regulations), and that it is signed by all subjects subsequently entered in the trial and those currently in the trial, if affected by the amendment.

### **11.8. Direct Access to Source Documentation**

Source data are all the information in original records and certified copies of original records of clinical findings, observations, or other activities in the study, which are necessary for the reconstruction and evaluation of the study. Source data are contained in source documents (originals or certified copies).

Source Documents are original documents, data, and records (e.g., clinical and office charts, laboratory notes, memoranda, subjects' diaries, pharmacy dispensing records, recorded data from automated instruments, copies or transcriptions certified after verification as being accurate and complete, subject files, and pharmacy records or prescriptions, laboratory reports or, computer printouts from the laboratory websites, vaccine handover sheet and delivery notes). All of them are expected to be reviewed signed, dated and assessed by investigator. The source documents must contain study participation information.

It is the Investigator's obligation to collect and present of all relevant medical data in the subject's medical file. Sponsor name and trial number, subject identification (name, date of birth, address, etc.), information that the informed consent was obtained prior any screening procedures, visit dates, subject number, vaccine information, efficacy data, safety data, concomitant medications and date and reason of completion of the study.

Source records should be preserved for the maximum period of time required by local requirements.

All information recorded on the eCRFs for this study must be consistent with the subject's source documentation.

Besides the monitor of the Contract Research Organization (CRO), regulatory authorities, members of ethics committees and the Sponsor's clinical quality assurance group or any other Sponsor's representative, may carry out source data checks and/or on-site audits or inspections. Direct access to source data will be required for these audits and inspections; they will be carried out giving due consideration to data protection and medical confidentiality. The investigator will assure the CRO and the sponsor of the necessary support at all times.

